**Figure 2 fig2:**

Timeline of the neuropsychological assessments and intervention. EIG, early intervention group; LIG, late intervention group.

Encoded pseudonymized patient data will be collected by assessors in paper questionnaires and standardized assessment forms to be transferred to Microsoft Excel and saved in a National Open Access Scientific Data Archive Information System (“MIDAS”)^1^ designed to collect and keep different research data as well as to secure accessibility of data and information in a digital environment. Data quality will be preserved by checking all data fields for missing values or errors upon completion of assessment. This task will be done by the investigators of the trial without the need for an external data monitoring committee because of the relatively small study sample.

The study is expected to last from January 2024 (start of patient recruitment) to late March 2026 (end of the intervention for the LIG). No interim analyses are planned.

### Sample size and statistical analysis

2.7.

The target sample size of the study was calculated for a between-group interaction of a two-way repeated measures analysis of variance (ANOVA) with *f* = 0.40, *α* = 0.05, *β* = 0.95, two groups (early and late intervention), three measurement points, and 0.5 correlation between repeated measures. The resulting sample size of *n* = 58 (G*Power 3.1.9.7) was increased by 20% to *n* = 70 to account for dropouts (including the possibility of patient referral to presurgical evaluation if needed according to principles of best medical practice) and corresponded well to the mean sample size and attrition rates in previous trials (5). This sample size is deemed achievable as the trial will be conducted in a large university hospital covering tertiary epilepsy care services for approximately 1.4 million of inhabitants and include a group of PWE composed of patients with both TLE and GGE.

The efficacy of the intervention will be defined as statistically significant improvement on one of the primary outcomes (quality of life or delayed memory), tested with a repeated-measures between-factors analysis of variance (ANOVA) in the EIG as compared to the LIG. For secondary analyses, dynamic changes of other outcome measures will be tested, respectively, by using ANOVA or ANCOVA. The association between demographic and clinical variables with study endpoints will be conducted by means of linear and ordinal regression modeling. Subgroup analyses are planned to be conducted based on sex, education status, professional status, epilepsy type, laterality and lesionality. In case of missing data, multiple imputation will be used in sensitivity analysis.

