Primary outcomes	Quality of life (Quality of Life in Epilepsy 31-item patient weighted version, QOLIE-31-P) 4 weeks post-intervention. Delayed verbal recall (Rey Auditory Verbal Learning Test, RAVLT) 4 weeks post-intervention. Delayed visual recall (Medical College of Georgia (MCG) Complex Figure test) 4 weeks post-intervention.
Key secondary outcomes	Symptoms of depression (Neurological Disorders Depression Inventory in Epilepsy, NDDI-E), anxiety (General Anxiety Disorder-7, GAD-7), stigma (Jacoby’s 3-item Stigma Scale).
Ethics review	Awaiting approval, Vilnius Regional Biomedical Research Ethics Committee
Completion date	2026-03-31 (estimated)
Summary results	Not applicable
Individual clinical trial participant-level data (IPD) sharing statement	No plan to share IPD

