### Participant recruitment, allocation, and timeline

2.6.

Study participants will be invited to participate in the trial during routine outpatient visits at the epilepsy clinic. They will have either temporal lobe or genetic generalized epilepsy as confirmed by the epileptologist, according to previously collected clinical (e.g., seizure semiology, patient history), instrumental (e.g., electroencephalography, video-electroencephalography), genetic and imaging (e.g., 3T magnetic resonance imaging) data required to substantiate the diagnosis according to guidelines by the International League Against Epilepsy. After acceptance, each new participant will be randomly assigned to either the early intervention group (EIG) or the late intervention group (LIG) at the time of enrolment by using open-source software for minimization (WinPepi) based on sex, epilepsy type and seizure control. The randomization will be done, and participants assigned to one of the groups by the principal investigator. Outcome assessors and data analysts will be blinded to participant status by using concealed patient coding and instructing patients not to discuss their status during examination. The principal investigator, psychologists performing the intervention and participants themselves will not be blinded.

Both the EIG and the LIG will undergo neuropsychological assessment at three time points (Figure 2). The EIG will be tested at baseline, with two follow-ups four and sixteen weeks after the intervention which itself lasts for eight weeks. The LIG will be tested at the same time points while on waitlist. Participants assigned to the LIG will be offered the intervention after the second follow-up. Both groups will receive otherwise routine clinical care (i.e., according to individual needs and best medical practice) at the tertiary epilepsy clinic. Given the non-invasive nature of the CoRE intervention, no adverse effects are expected. Therefore, discontinuation of the intervention is expected to occur only in the case of participant dropout. Patient attrition will be minimized by thoroughly discussing the aims and procedures of the trial before enrolment as well as by accommodating to the patients’ availability and daily schedule for the weekly sessions.

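### The n = 58 attributed to an interaction is the answer for a group main effect that counts baseline, so the stated 95% power rests on an undisclosed 1.2 SD effect at both follow-ups

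*Protocol article*

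**What the plan says.** Section 2.7 of the protocol article gives the target test as follows: "The target sample size of the study was calculated for a between-group interaction of a two-way repeated measures analysis of variance (ANOVA"). The inputs are "with *f* = 0.40, *α* = 0.05, *β* = 0.95, two groups (early and late intervention"), then "three measurement points, and 0.5 correlation between repeated measures". The result is reported thus: "The resulting sample size of *n* = 58 (G*Power 3.1.9.7) was increased by 20% to *n* = 70 to account for dropouts".

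The next paragraph of section 2.7 has efficacy "tested with a repeated-measures between-factors analysis of variance (ANOVA) in the EIG as compared to the LIG".

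Two other places bear on what is being powered. Section 2.6 shows that the first of the three measurements precedes treatment: "The EIG will be tested at baseline, with two follow-ups four and sixteen weeks after the intervention which itself lasts for eight weeks". Table 1 in section 2.1 sets each of the three primary outcomes at a single time, for example "Delayed verbal recall (Rey Auditory Verbal Learning Test, RAVLT) 4 weeks post-intervention".

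**The concern.** Section 2.7 names an interaction for the sample size and a between-factors test for efficacy. These are different tests with different noncentrality parameters, and one n cannot be the minimum for both at the same f. If the figure belongs to the main effect, it concerns each group's average over all three visits. One of those visits is a baseline at which no difference is expected, and none of the primary outcomes is defined as such an average.

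At stake is what the 95% means. A reader will take it as the power to detect the 4-week benefit in Table 1, but section 2.7 never says how large that benefit is assumed to be. The symbol is also wrong: β is the type II error, so a β of 0.95 would literally mean power of 1 − 0.95 = 5%.

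**Working it through.** **Inputs.** From section 2.7: f = 0.40, alpha = 0.05, target power 0.95 (reading the β as power), two groups, m = 3 measurements, correlation ρ = 0.5. From section 2.6: measurement 1 is baseline. Assumed, because no ratio is stated: equal groups, so N is even. Power comes from the noncentral F or t distribution.

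**1. Reproducing 58.** Between-factors group main effect, df 1 and N − 2:

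λ = f²·N·m / (1 + (m − 1)ρ) = 0.16 × 3 / 2 × N = 0.24N

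- N = 56: 94.95%
- N = 57: 95.3%
- N = 58: 95.6%

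The smallest even N reaching 95% is 58, exactly the stated figure.

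**2. The interaction as labelled**, df 2 and 2(N − 2):

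| Effect-size definition | λ | N for 95% | Power at N = 58 |
|---|---|---|---|
| Default, f²Nm/(1 − ρ) | 0.96N | 18 (95.3%; N = 16 gives 92.4%) | above 99.9% |
| f²N(m − 1) | 0.32N | 50 (95.1%) | 97.5% |
| f²(N − 2)(m − 1) | 0.32(N − 2) | 52 (95.1%) | 97.0% |

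Other settings were tried as well. A multivariate test gives 20, a sphericity correction of 0.5 gives 30, ρ = 0 gives 34, and the bare form λ = f²N gives 100. None gives 58.

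**3. What f = 0.40 implies for the main effect.** With two groups the standardised difference is 2f = 0.8 SD, here the average over the three visits. With zero expected at baseline and δ at each follow-up:

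(0 + δ + δ)/3 = 0.8, so δ = 1.2 SD

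A 1.2 SD difference at week 4 would give an unadjusted 4-week t test at N = 58 a power of 99.4%. Read instead as an interaction on the default definition, f = 0.40 implies about 1.7 SD at both follow-ups: a 0.8 SD pattern (0, 0.8, 0.8) has an interaction f of 0.1886, and 0.8 × 0.40/0.1886 ≈ 1.7.

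**4. If 0.8 SD at follow-up was meant (an assumption).** Between-factors test, N = 58, λ = f² × 58 × 1.5:

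| Differences at baseline, week 4, week 16 | Average (SD) | f | Power |
|---|---|---|---|
| 0, 0.8, 0.8 (sustained) | 0.533 | 0.267 | 68.6% |
| 0, 0.8, 0.4 (halved) | 0.400 | 0.200 | 45.0% |
| 0, 0.8, 0 (week 4 only) | 0.267 | 0.133 | 23.1% |

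Other tests of the same 0.8 SD at N = 58:

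- Default interaction, sustained effect: λ = 0.1886² × 6 × 58 = 12.4; power 88.4%.
- Unadjusted 4-week t test: noncentrality 0.8 × √(29/2) = 3.05, df 56; power 84.9%.
- Baseline-adjusted 4-week ANCOVA: residual variance 1 − 0.5² = 0.75, effect 0.8/√0.75 = 0.924, noncentrality 3.52, df 55; power 93.3%.

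If all 70 complete, the between-factors test (sustained effect) has 76.9%, the t test 91.0% and the ANCOVA 96.8%.

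**5. The uplift.** 58 × 1.2 = 69.6, so 70 follows as stated.

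**The case against.** The best defence is that nothing is short on the protocol's own inputs. At f = 0.40, 58 gives 95.6% for the between-factors test and at least 97% for the interaction under the default and both alternative definitions. The test that was computed is also the one section 2.7 names for efficacy, so one word is wrong. This stands, and it limits the point to a mislabelled test and an undisclosed effect size.

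A reader might infer more: that the trial lacks 95% power for its 4-week endpoint. The documents do not support that. The shortfalls in step 4 arise only if f = 0.40 stood for 0.8 SD at follow-up, and the protocol does not say what difference f represents. Taken literally, the 1.2 SD it implies would give ample 4-week power.

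A reader might also fault the 20% uplift for covering only 12/70 = 17% loss. Section 2.7 says the number was raised by 20%, which it was, and it does not promise to absorb 20% attrition. At 20% loss, 56 completers would still have 94.95% on the computed test.

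The defence does not answer why a 4-week endpoint is powered through an average that includes a pre-treatment visit, or where section 2.7 discloses the 1.2 SD this requires.

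**Conclusion.** The point holds as a labelling error together with an effect size that is not disclosed. The figure of 58 is reproduced exactly by the group main effect and by no form of the interaction that was tried. The stated 95% is true of a three-visit average, requires 1.2 SD at both follow-ups if baseline is balanced, and is not tied to the 4-week outcomes in Table 1.

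How far this matters depends on the intended effect. At 1.2 SD there is no power problem. At 0.8 SD, power with 58 completers runs from 69% (between-factors, sustained effect; 45% if halved at week 16, 23% if confined to week 4) through 85% (unadjusted 4-week comparison) to 93% (baseline-adjusted 4-week comparison). These figures assume equal groups, a correlation of 0.5, an alpha of 0.05 and a single outcome. They do not show n = 70 to be inadequate for a baseline-adjusted 4-week analysis.

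**What to change.** Leave n = 70 and the 20% uplift as they are, and rewrite the sample-size paragraph of section 2.7:

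- Replace the interaction label with the test actually computed, and give 0.95 as power (1 − β).
- Name the baseline-adjusted group difference at 4 weeks as the primary contrast, in agreement with Table 1.
- State the assumed effect as a standardised difference at 4 weeks, with its justification.
- Report the power for that contrast, for example about 93% at alpha 0.05 for 0.8 SD, correlation 0.5 and 58 completers. Use whatever alpha the trial adopts for its three primary outcomes.

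The cost is one rewritten paragraph, a matching change to the efficacy test in the same section, and probably a somewhat less favourable stated power. No further participants are needed.

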## Introduction

1.

Epilepsy is a multifaceted chronic neurologic disorder that occurs in every hundred individuals and directly affects patients’ cognition, quality of life as well as professional and societal activities (1). Because of premature mortality, mental health and socioeconomic implications of this disorder, it is now also recognized as a global public health priority by the World Health Organization (2). Cognitive dysfunction is a major burden for people with epilepsy (PWE) as epilepsy limits their ability to remember, learn, focus, and think. It has been shown that a third of newly diagnosed PWE have subjective cognitive complaints, and up to one half perform worse than controls during objective neuropsychological evaluation (3). Epilepsy can affect various cognitive domains, such as memory or attention, with a possible increase in the level of impairment over time (4). While the problem of prevalent cognitive dysfunction is well-known and may have significant impact on quality of life and social functioning in epilepsy, studies investigating the feasibility and efficacy of cognitive rehabilitation in epilepsy (CoRE) are rare: just nine group studies were identified in the most recent systematic review (5). Importantly, most were of only moderate quality. The lack of new studies of CoRE is seen as a significant shortcoming of modern epileptology: this neglect is thought to stem from a lack in resources and a historical focus on seizure control rather than cognitive outcomes in the clinical setting (6).

We aim to conduct a novel randomized waitlist-controlled cross-over trial of an original CoRE program, assess its overall efficacity and determine factors associated with a better response to this intervention. The main hypothesis of the trial is that a combined individual and group CoRE program is effective in improving quality of life and verbal as well as visual memory in PWE.

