### Outcomes

2.5.

The primary outcome of the intervention will be measured by its effects (1) on quality of life and (2) memory function.

Changes in quality of life among PWE enrolled in the study will be estimated by comparing scores of the Quality of Life in Epilepsy 31-item inventory (patient weighted version, QOLIE-31-P) that has been validated in Lithuania and is among the most frequently used standardized quality of life assessment tools in PWE (9, 10). By selecting quality of life as the primary endpoint, we intend to detect broader effects of the intervention (i.e., beyond objective cognitive performance) representing direct benefits to participating PWE.

Verbal memory will be assessed by using the Lithuanian equivalent of the Rey Auditory Verbal Learning Test (RAVLT) that consists of five learning trials of a 15-word list A, one learning trial of a word list B and measuring the delayed recall of the word list after 30 min (11). Visual recall at 30 min will be measured by using the Medical College of Georgia (MCG) Complex Figure test for repeated testing (12).

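### Efficacy is declared if any one of three primary outcomes improves, with no multiplicity adjustment in the protocol: familywise error about 11–14% rather than 5%, false claims of benefit about 5.5–7.3% rather than 2.5%

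*Protocol article*

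**What the plan says.** Table 1 (section 2.1) gives three primary outcomes, each with its own instrument and the same time point. The first entry reads "Quality of life (Quality of Life in Epilepsy 31-item patient weighted version, QOLIE-31-P) 4 weeks post-intervention". The second, on verbal memory, reads "Delayed verbal recall (Rey Auditory Verbal Learning Test, RAVLT) 4 weeks post-intervention". The third, on visual memory, reads "Delayed visual recall (Medical College of Georgia (MCG) Complex Figure test) 4 weeks post-intervention".

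Section 2.5 groups them into two domains: "The primary outcome of the intervention will be measured by its effects (1) on quality of life and (2) memory function". It then measures memory with two separate tests, one verbal and one visual.

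Section 2.7 defines success: "The efficacy of the intervention will be defined as statistically significant improvement on one of the primary outcomes (quality of life or delayed memory"). The same sentence says that this is to be "tested with a repeated-measures between-factors analysis of variance (ANOVA) in the EIG as compared to the LIG". The only alpha in the article is 0.05. It appears once, as an input to a sample size for a single test with "two groups (early and late intervention), three measurement points, and 0.5 correlation between repeated measures". No split of alpha, order of testing or adjusted threshold is given. Section 2.6 plans no interim analyses, so no alpha is spent there.

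The Introduction states the main hypothesis: that the programme is "effective in improving quality of life and verbal as well as visual memory in PWE".

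**The concern.** A rule that succeeds on any one of several outcomes gives the trial several chances of a false positive. The sample size section uses 0.05 for one test, and that figure no longer describes the error rate of the trial's success criterion once three tests can each satisfy it.

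The rule and the hypothesis also differ in strength. The hypothesis joins quality of life, verbal memory and visual memory; the rule is met by one of them. A trial with both memory outcomes null could report the intervention as efficacious on quality of life alone, without breaking its own plan.

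**Working it through.** **Inputs from the article.** Three primary outcomes (Table 1); success on any one, in the direction of improvement (section 2.7); alpha 0.05, f = 0.40, two groups, three time points, correlation 0.5 over time, n = 58 raised by 20% to 70 (section 2.7). The 0.95 printed as β works only as power.

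**Assumptions.** Each outcome is tested at two-sided 0.05, allocation is 1:1, and the three test statistics have a common correlation r. The article gives no r, so a range is shown.

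**Step 1: reproduce n = 58.** The repeated-measures, between-factors calculation has noncentrality λ = f²·N·m/(1+(m−1)ρ), with 1 and N−2 degrees of freedom. With N = 58, λ = 0.16 × 58 × 3/(1 + 2 × 0.5) = 13.92, and power at alpha 0.05 is 95.6%. N = 56 gives 94.95%, just short of 95%. So 58 is reproduced, for one outcome at 0.05. The text calls this a between-group interaction, but the interaction option gives N = 18; the figure comes from the between-factors option. Also 58 × 1.2 = 69.6, hence 70.

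**Step 2: error rate of the any-one rule.** For independent outcomes:

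- any significant difference: 1 − 0.95³ = 14.3%
- significant and favouring the early group: 1 − 0.975³ = 7.3%

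For correlated outcomes, from the equicorrelated normal distribution:

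| r | Three outcomes, either direction (single test 5%) | Three outcomes, favourable only (single test 2.5%) | Two outcomes, either direction | Two outcomes, favourable only |
|---|---|---|---|---|
| 0 | 14.3% | 7.3% | 9.75% | 4.9% |
| 0.3 | 13.6% | 6.8% | 9.5% | 4.8% |
| 0.5 | 12.5% | 6.3% | 9.1% | 4.5% |
| 0.7 | 10.9% | 5.5% | 8.3% | 4.2% |

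The two-outcome columns apply only if memory counted as a single outcome.

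**Step 3: check with the ANOVA itself.** Simulated repeated-measures ANOVAs with N = 58 (40,000 trials) gave 14.0–14.4% at r = 0, 13.7% at r = 0.3 and 12.8–12.9% at r = 0.5 for any significant result, in line with the table.

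**Step 4: power after adjustment.** Holm compares the smallest p-value with 0.05/3 = 0.0167, the next with 0.025 and the largest with 0.05. With the formula of step 1:

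- 58 completers, alpha 0.05: 95.6%
- 58 completers, alpha 0.025: 92.0%
- 58 completers, alpha 0.0167: 89.3%
- 70 completers (λ = 0.16 × 70 × 3/2 = 16.8), alpha 0.0167: 94.7%

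Reaching 95% at 0.0167 would take 72 completers, or 72 × 1.2 = 86.4, so 87 recruited.

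**The case against.** **A reader might infer that the chance of a false efficacy claim is 13–14%.** The article does not support this. Its rule requires improvement in the early group relative to the late group, so a significant result favouring the waitlist is not a success. The figure that matches the rule is 5.5–7.3% against 2.5%. The 13–14% is a two-sided familywise error, and it holds only at low between-outcome correlations (about 0 to 0.4). A higher directional figure, about 9–10%, arises only if the two-degree-of-freedom interaction test is used and a favourable change at either follow-up counts as improvement.

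**The number of primary outcomes is not fully settled.** Section 2.5 speaks of two domains and also calls quality of life the primary endpoint in the singular; section 2.7 names quality of life or delayed memory. Counting two outcomes lowers the figures to about 8–10% and 4–5%. This stands as a qualification, but memory is measured by two tests, Table 1 lists them separately, and nothing says how they would be combined.

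**An analysis plan that is not shown may contain an adjustment.** That is possible, so the finding is that none appears in this document, not that the trial has none. The point survives because the protocol is not silent: it fixes the success rule itself, and the rule as published permits an unadjusted claim.

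**A reader might infer that the rule contradicts the hypothesis, or that one positive outcome would be taken to confirm all three.** The article says neither. The hypothesis lists the expected effects; the rule says when efficacy is declared. They are mismatched in strength, and that is as far as the text goes.

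**Participants know their allocation and QOLIE-31-P is self-reported.** This is a question of blinding. Holm alone would still allow a claim on quality of life; only outcome-by-outcome wording keeps such a claim within its scope. Outcome assessors are blinded (section 2.6).

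**Conclusion.** The point holds. The protocol fixes an any-one success rule over three listed primary outcomes and states no adjustment, while its sample size treats 0.05 as the level of a single test. Under that rule the familywise error is 10.9–14.3% instead of 5%, and the chance of a false claim of benefit is 5.5–7.3% instead of 2.5%: a two- to threefold inflation on either scale. This rests on testing each outcome at two-sided 0.05, which the article implies through its sample size but does not state for the primary tests, and on between-outcome correlations of 0 to 0.7. Because the defect lies in the definition of trial success, it should be settled before any unblinded analysis.

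**What to change.** Replace the efficacy sentence in section 2.7 with wording to this effect: the familywise type I error is controlled at two-sided 0.05 across QOLIE-31-P, RAVLT delayed recall and MCG delayed recall with Holm's procedure; efficacy is claimed separately for each outcome that passes in favour of the early group; the full hypothesis of the Introduction is claimed only if all three pass. Align section 2.5 with Table 1 so that the number of primary outcomes is the same throughout. If an analysis plan already contains an adjustment, the protocol text should be made to match it.

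The change needs no new data or visits. Its cost is power. At the protocol's assumed effect, an outcome that must pass the strictest Holm step has 89.3% power with 58 completers and 94.7% if all 70 complete, instead of 95.6% with 58 at alpha 0.05. The stated 95% should be restated accordingly. The all-three claim is harder: even at an unadjusted 0.05, three independent outcomes would give 0.956³ = 87.4% with 58 completers; Holm gives somewhat less, and positive correlation between outcomes would raise it. Keeping 95% at the strictest step would take 72 completers, but the planned sample supports the adjusted tests well enough that no increase is needed.

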**Figure 1 fig1:**
[figure not shown]
An example of a figure used in the experimental memory task. The figure will serve as a learning aid to memorize items of one week’s schedule, including place, time, and activity, as they are being read by the investigator. Participants will be asked to recall the same data after 30 min.

The possible learning effects at post-interventional follow-ups will be mitigated by using three different versions of the same memory tests as well as by comparing memory function in late vs. early intervention groups rather than improved performance in comparison to baseline scores in each subgroup.

BOX 1Outline of the content of the CoRE intervention.CoRE intervention plan (8 weeks)1. Individual session.■ Familiarization.■ Goal setting. Discussion of the plan.■ Presentation of the Mind-Emotion-Body connection.■ Homework.2. Individual session.■ Discussion of homework.■ Thought exercises.■ Thinking training. Visual memory.■ Homework.3. Individual session.■ Discussion of homework.■ Body senses. Attention training.■ Physiology training.■ Homework.4. Individual session.■ Discussion of homework.■ Working with emotions. Influence of emotions on quality of life and memory.■ Emotion regulation.■ Memory training.■ Homework.5. Individual session.■ Discussion of homework.■ Attention management.■ Metacognition training.■ Self-regulation.■ Homework.6. Individual session.■ Discussion of homework.■ Positive psychology.■ Strengths and resources.■ Memory training.■ Homework.7. Group session.■ Discussion of homework.■ The importance of social support.■ Creating a circle of support.■ Attention training.■ Homework.8. Group session.■ Discussion of homework.■ Compassion for self and others.■ Memory and quality of life.■ Homework. Summing up.General plan of a 60-min session:■ 10 min: presentation of the topic and discussion of homework.■ 20 min: teaching of the topic.■ 20 min: skill building.■ 10 min: reflection. Questions. Homework.

Demographic (sex, age, educational and professional status, personal relationship status, socioeconomic status) and clinical (seizure type, epilepsy type, epilepsy etiology, epilepsy duration, seizure frequency, antiseizure medications used, seizure and electroencephalography laterality, localization of seizure focus (if present), handedness, somatic comorbidities) data of each participant will be collected to predefined case report forms.

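### The primary outcomes are set at 4 weeks, but the primary ANOVA does not isolate that visit, and the test is named in two ways that do not agree

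*Protocol article*

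**What the plan says.** Table 1 of the protocol article (Trial registration) fixes each primary outcome at one visit. For verbal memory it reads "Delayed verbal recall (Rey Auditory Verbal Learning Test, RAVLT) 4 weeks post-intervention"; the quality-of-life score and delayed visual recall carry the same time point.

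The section on recruitment, allocation and timeline gives the visits: "The EIG will be tested at baseline, with two follow-ups four and sixteen weeks after the intervention which itself lasts for eight weeks". The late intervention group (LIG) is assessed at the same three points and is on the waitlist throughout.

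The section on sample size and statistical analysis then names the test twice. Efficacy is a significant improvement on one of the primary outcomes, "tested with a repeated-measures between-factors analysis of variance (ANOVA) in the EIG as compared to the LIG". The sample size, however, was "calculated for a between-group interaction of a two-way repeated measures analysis of variance (ANOVA"). Its inputs are an effect size f of 0.40, a 5% significance level, 95% power and two arms; for the visits, the article assumes "three measurement points, and 0.5 correlation between repeated measures". It then arrives at the total as follows: "The resulting sample size of *n* = 58 (G*Power 3.1.9.7) was increased by 20% to *n* = 70 to account for dropouts". ANCOVA is mentioned only for secondary analyses.

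The Outcomes section says that learning effects will be limited partly by "comparing memory function in late vs. early intervention groups rather than improved performance in comparison to baseline scores in each subgroup".

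**The concern.** A between-factors effect in a three-visit ANOVA compares the two groups on the mean of all three visits. Baseline precedes treatment, so under randomisation its expected group difference is zero, and one third of the tested contrast carries no treatment effect. The 16-week value, which is not the declared endpoint, makes up another third.

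If the interaction was meant, the test asks whether the groups' profiles differ in any way over three visits (2 degrees of freedom). Baseline then serves as a reference and does not dilute the effect, but the 4-week difference is still not singled out.

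At stake are the estimate, which under the main-effect reading understates the benefit at the declared visit, and the chance of detecting a real 4-week benefit, particularly one that fades.

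**Working it through.** **Inputs from the article.** f = 0.40; alpha = 0.05; power 0.95 (printed as β); 2 groups; m = 3 visits; correlation ρ = 0.5; N = 58, raised to 70.

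**Step 1: reproduce N = 58** (noncentral F).
- Between-factors main effect: λ = f²·N·m / (1 + (m − 1)ρ), df 1 and N − 2. At N = 58, λ = 0.16 × 58 × 3 / 2 = 13.92 and power is 0.956. N = 56 gives 0.9495, so 58 is the exact answer.
- Within-between interaction, G*Power default: λ = f²·N·m / (1 − ρ), df 2 and 2(N − 2). The requirement is N = 18 (λ = 17.28, power 0.953).
- Other conventions for the interaction effect size give 52, 100 or 102. None gives 58.
- Dropout: 58 × 1.2 = 69.6, rounded to 70.

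**Step 2: what the main effect estimates.** With group differences (0, d, d) at the three visits, the contrast is (0 + d + d)/3 = 2d/3, whatever the correlation. For d = 0.8 it is 0.533, so f falls from 0.40 to 0.533/2 = 0.267. For the visit-averaged f to be 0.40, the difference at both follow-ups would have to be d = 1.2, since (0 + 1.2 + 1.2)/3 = 0.8 = 2f.

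**Step 3: power at N = 58.** Assumptions made here: d = 0.8 (= 2f) at 4 weeks, zero difference at baseline, compound symmetry. The article gives no raw difference, SD or effect pattern.

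- Main effect: λ = (N/4)·(mean difference)² / [(1 + 2ρ)/3]. Sustained: 14.5 × 0.2844 / 0.6667 = 6.19. Halved to 0.4 at week 16: 14.5 × 0.16 / 0.6667 = 3.48.
- Interaction: λ = (N/4)·(sum of squared deviations of the three differences from their mean) / (1 − ρ). Sustained: 14.5 × 0.4267 / 0.5 = 12.37. Halved: 14.5 × 0.32 / 0.5 = 9.28.
- ANCOVA at 4 weeks: λ = (N/4)·d² / (1 − ρ²), df 1 and N − 3: 14.5 × 0.64 / 0.75 = 12.37 in both patterns.

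| Pattern of differences | ρ | Main effect | Interaction (2 df) | ANCOVA at 4 weeks |
|---|---|---|---|---|
| 0, 0.8, 0.8 | 0.3 | 78% | 75% | 88% |
| 0, 0.8, 0.8 | 0.5 | 69% | 88% | 93% |
| 0, 0.8, 0.8 | 0.8 | 57% | 99.9% | 99.9% |
| 0, 0.8, 0.4 | 0.5 | 45% | 77% | 93% |

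**Step 4: sample size at ρ = 0.5 for 95% power.** ANCOVA at 4 weeks needs 64 completers. The main effect needs 124 if the effect is sustained and 220 if it halves. With all 70 retained, the sustained case gives 77% for the main effect and 97% for ANCOVA.

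**The case against.** A reader might infer that the plan certainly averages baseline into its primary test and so certainly loses much of its power. The article does not support that as fact. Its sample-size sentence names an interaction, and its efficacy definition speaks of improvement in one group relative to the other, which reads naturally as a group-by-time effect. Reproducing 58 shows which formula was used for planning; it does not prove which effect will be tested. Under the interaction reading the loss against ANCOVA at ρ = 0.5 is 5 points if the effect is sustained (88% against 93%), and at ρ = 0.8 there is none. This objection stands, and the point is worded accordingly.

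The d = 0.8 is also an assumption. If f = 0.40 is taken as the visit-averaged difference, the main effect has its planned 95.6%. But that requires d = 1.2 at both follow-ups, which the article does not claim.

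It is tempting as well to blame the 16-week visit. That holds only if the effect fades. If it is sustained, the baseline-adjusted average of both follow-ups has about 99% power (λ = 14.5 × 0.64 / 0.5 = 18.56), more than 4 weeks alone. In the sustained case the loss comes from baseline.

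The remark on learning effects in the Outcomes section should not be read as ruling out baseline adjustment. It rejects judging change within each group. Baseline as a covariate still compares the groups at the same visit, so practice effects common to both cancel.

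Finally, visit-specific contrasts are often left to an analysis plan. But the article itself names the test that defines efficacy, and under neither of its two names does that test isolate the declared endpoint. That is a mismatch within the text, not an omitted detail.

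**Conclusion.** The point holds in this form: the declared 4-week endpoint and the named primary test do not match under either reading, and the two names for the test conflict. Of the calculations tried, only the between-factors main effect yields 58.

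Under that main effect, a sustained effect is estimated at two thirds of its size, whatever the correlation. The power loss depends on assumptions. For d = 0.8, 58 completers and ρ = 0.5, it is 24 points against a 4-week ANCOVA if the effect is sustained (93 − 69) and 48 points if it halves by week 16 (93 − 45). Over ρ = 0.3 to 0.8 in the sustained case, the loss runs from 10 points (88 − 78) to about 43 (99.9 − 57). Under the interaction reading, the losses at ρ = 0.5 are 5 and 16 points, and 58 does not follow from the stated inputs.

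The type I error of the named test is not affected. What is affected is the quantity estimated and the chance of detecting a real 4-week benefit.

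**What to change.** - Make the single primary test for each outcome the baseline-adjusted difference between the early and late groups at 4 weeks post-intervention. Use ANCOVA, or a mixed model with group-by-visit terms from which the 4-week contrast is taken.
- Make the 16-week contrast secondary, as the test of maintenance.
- Use one name for the primary test throughout the section on sample size and statistical analysis.
- Restate the sample-size basis for that test. With d = 0.8 and ρ = 0.5, power is about 93% with 58 completers, 95% with about 64, and 97% if all 70 complete.

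Cost: the wording and the sample-size paragraph change, and the stated power at 58 completers falls slightly below 95%. Baseline is already collected, and no extra patients or visits are needed.
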